#### Process for Contacting and Recruiting Patients

The list of eligible patients that was extracted from each home support provider database contains patient contact details (ie, email address or smartphone number). This list is uploaded into [name] and an algorithm checks the validity of the contact details. Eligible patients with valid contact information receive an email or SMS invitation to connect to this platform for the consent process. The invitation does not include sensitive data.

An explanatory video is provided, within the [name] account of each patient, to ensure that potential participants fully understand the study’s aims, procedures, and their rights.

Those who provide consent are granted access to the ePRO tool and invited to complete the questionnaire, which should take them an estimated 10 minutes.

### Ethical Considerations

The study protocol was developed in collaboration with a scientific committee composed of experts in OSA and methodologists from the 4 countries involved. The regulatory process and patient consent for a study with the reuse of data and a questionnaire were different for the 4 countries.

In France, the study followed the methodology MR-004 of the French Data Protection Authority (Commission Nationale Informatique et Liberté) concerning research that reuses data that have already been collected [33] and was approved by the local ethics committee of Angers University Hospital in November 2023 (2023-159). In Portugal, the study was considered observational and required approval by a central ethics committee; the approval was obtained from the ethics committee of Lisboa in May 2024 (24/24). In Spain, the study was considered observational and required approval by the ethics committee at each participating hospital; approval was obtained from the CEIm Hospital Universitario Ramón y Cajal of Madrid in July 2024 (095/24) and from the CEIm Hospital Universitario Doctor Peset of Valencia in December 2024 (127/24) and is pending for other regions. In Belgium, the study was considered interventional and required approval by a central ethics committee (Commissie voor Medische Ethiek Ziekenhuisnetwerk Antwerpen Institutional Review Board, Ziekenhuis aan de Stroom Middelheim) and by the local ethics committee at each participating hospital. Ethics approvals from the belgian central ethics committee are still pending.

In France, potential participants have the option to decline the reuse of their personal data through an “opt-out” process. Conversely, in Belgium, Portugal, and Spain, an “opt-in” process has been established, requiring explicit consent from participants to join the study.

No compensation is provided to participants.

### Outcome Measures

Study outcomes, time points, and data sources are summarized in Table 1. An ePRO tool will be used to administer the patient questionnaire. The ePRO tool was designed to assess various aspects of a patient’s status, condition, and experience at 2 time points: the time of ePRO completion and the beginning of PAP therapy. This included sociodemographic characteristics (age, relationship status, employment, education level, and social support), health status (BMI, smoking status, alcohol intake, comorbidities, sleep duration, and use medications to aid sleep), OSA-related factors (when PAP therapy was started, apnea-hypopnea index before starting PAP, and OSA symptoms), PAP therapy experience and satisfaction (tolerability of PAP, attitude to PAP, device noise, and level of motivation to use PAP), patient experience and satisfaction with home support providers, quality of life (including current health status), and OSA-PAP literacy. The full ePRO questionnaire is provided in Multimedia Appendix 1.

Home support provider service will be assessed using 4 components: frequency of interactions between the home support provider and a patient; content of support (logistical, educational, supportive, or behavioral); personalization of support according to patient profile or needs; and telemonitoring (telemetry, data visualization, and alerts triggering home support provider interventions).

**Table 1 table1:** Study outcomes.

Category and outcome		Time points	Source

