**Home support provider PAP-related service**			
	Number and type of interactions (home visit, phone call, and digital interaction) Number of mask changes Implementation of telemonitoring	1, 4, 6, and 12 months after starting PAP therapy and annually thereafter	ALH ERP

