#### Statistical Analysis

Statistical analyses will be performed according to a predefined statistical analysis plan (Table 2).

**Table 2 table2:** Statistical analysis plan details.

Objectives	Main outcomes	Key explanatory variables	Statistical methods
Compare PAP^a^ adherence and the PAP therapy persistence rate between different levels of home support provider service	PAP adherence: (1) mean number of hours/day of PAP use and (2) adherent patients defined as those with mean PAP use ≥4 hours/day PAP persistence: (1) percentage of days with PAP use, (2) patients still in therapy, and (3) patients still in therapy and adherent	Fixed effect: Level of service (standard of care, personalized care plan, or high service level) Random effect: Country	Multilevel model adjusted for selected confounding factors
Identify service components that influence PAP adherence and persistence	PAP adherence: (1) mean number of hours/day of PAP use and (2) adherent patients defined as those with mean PAP use ≥4 hours/day PAP persistence: (1) percentage of days with PAP use, (2) patients still in therapy, and (3) patients still in therapy and adherent	Fixed effect: Frequency of interactions, content of support, personalization of support, and telemonitoring Random effect: Country	Multilevel model adjusted for selected confounding factors
Identify factors associated with PAP adherence and persistence	PAP adherence: (1) mean number of hours/day of PAP use and (2) adherent patients defined as those with mean PAP use ≥4 hours/day PAP persistence: (1) percentage of days with PAP use, (2) patients still in therapy, and (3) patients still in therapy and adherent	Fixed effect: Frequency of interactions, content of support, personalization of support, telemonitoring, sociodemographic characteristics, OSA^b^-related clinical characteristics, and characteristics of PAP therapy Random effect: Country	Multilevel model
Descriptive Analysis	Sociodemographic characteristics OSA-related clinical characteristics OSA and PAP literacy Experience with PAP therapy Experience with home support provider support Quality of life Home support provider PAP-related service	N/A^c^	Usual descriptive statistics: Analysis by country
Describe patterns of PAP use	Mean PAP use categories over time	N/A	Data visualization such as Sankey diagrams

^a^PAP: positive airway pressure.

^b^OSA: obstructive sleep apnea.

^c^N/A: not applicable.

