## Discussion

### Study Rationale

The high and increasing number of patients with OSA treated with PAP therapy drives concerns among health systems regarding the associated health care resource consumption and costs. This has led some countries to implement significant changes in the patient pathway, notably toward more home-centered models [30,46]. Regardless of the care setting, PAP adherence and persistence are essential because they are associated with health benefits [19], whereas poor adherence and PAP therapy terminations have been associated with increased disability, health care resource consumption, and direct or indirect costs [47-49].

Despite a large body of evidence regarding the factors associated with PAP adherence [50] and persistence [25,51], and the reimbursement of PAP-related services in many European Union countries, there is currently a lack of evidence regarding the impact of home support provider services on these outcomes. In addition, although defined by country or local regulations, the level of home support provider service is poorly described. Differences exist in service frequency, content, and communication channels between home support providers and patients, the use of PAP telemonitoring, and the qualifications of home support provider personnel. Some of these components have been shown to impact PAP adherence [29,30,52,53].

Our working hypothesis is that a higher level of home support provider service would be associated with better PAP adherence and persistence. This study will also investigate between-country differences in terms of patient characteristics, OSA-related characteristics, and services, and identify which components of service are most effective at improving adherence and persistence.

We anticipate that this research will provide valuable evidence to inform decision-making by authorities and payers regarding the regular reassessment of services and associated tariffs. It could also support guidelines relating to the follow-up of individuals receiving PAP therapy.

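### If frequency of interactions is the realised contact count, the component model (Table 2, second row) gives the effect of telemonitoring at a given number of contacts, not the effect of implementing it

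*Protocol article*

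**What the plan says.** Outcome Measures in the protocol article splits home support provider service into four components. One is "frequency of interactions between the home support provider and a patient". Another is "telemonitoring (telemetry, data visualization, and alerts triggering home support provider interventions". Prompting provider action is therefore part of telemonitoring as the plan defines it.

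Table 1, under home support provider service, lists "Number and type of interactions (home visit, phone call, and digital interaction", followed by mask changes and implementation of telemonitoring. All are recorded at "1, 4, 6, and 12 months after starting PAP therapy and annually thereafter". Interactions are classified by channel. Whether a contact was scheduled or prompted by an alert is not mentioned.

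Table 2, second row (service components), specifies "Fixed effect: Frequency of interactions, content of support, personalization of support, and telemonitoring", with country as a random effect and adjustment for selected confounders. The third row (associated factors) contains the same four components plus patient and therapy characteristics. The first row (the main comparison) uses the level of service instead and has no term for contacts.

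On purpose, Study Objectives seeks components that influence adherence and persistence, and Study Rationale says the study will "identify which components of service are most effective at improving adherence and persistence", with payers and tariff decisions in view.

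**The concern.** If alerts lead to calls or visits, some contacts are a consequence of telemonitoring. Entering the realised number of contacts beside telemonitoring adjusts for a mediator. The telemonitoring coefficient then answers this question: among patients with the same number of contacts, how does use differ with and without telemonitoring? A payer deciding whether to fund telemonitoring asks a different one: what happens to use when it is introduced, including the contacts that its alerts generate?

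The two answers can differ widely. In the simplest case, telemonitoring could raise use entirely through prompted contacts and still show a coefficient near zero, with the benefit credited to frequency. A large sample does not help, because it only makes the estimate of a different quantity more precise. The e-value analysis addresses unmeasured confounding, and the COVID-19 and device-recall sensitivity analyses leave both terms in the model, so none of these covers the problem.

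**Working it through.** The plan states no figure on this point, so there is none to reproduce. The article gives no effect per contact, no number of alert-prompted contacts and no standard deviation. Every value below is an assumption chosen for illustration.

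**Algebra.** Let T be telemonitoring (0/1), M the number of contacts and Y mean hours per day. Suppose Y = constant + a·T + b·M + error, that T adds d contacts on average, and that contacts are unrelated to prior use.

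- Effect of implementing telemonitoring: a + b·d.
- Coefficient of T with M in the model: a.
- Difference: b·d, the part delivered through contacts.

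With d = 2, three combinations give the same total of 0.30 h/day:

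| Case | a | b | Total a + 2b | Coefficient given M | Part omitted |
|---|---|---|---|---|---|
| A | 0.10 | 0.10 | 0.30 | 0.10 | 0.20 (67%) |
| B | 0.00 | 0.15 | 0.30 | 0.00 | 0.30 (100%) |
| C | 0.20 | 0.05 | 0.30 | 0.20 | 0.10 (33%) |

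**Simulation.** 400,000 patients were simulated in four countries, with telemonitoring in 90%, 20%, 40% and 50% of patients. Scheduled contacts were Poisson with mean 4. Alert-prompted contacts averaged 2 per telemonitored patient. A latent tendency to low use (standard deviation 1) lowered Y by 1 h/day per unit, and the residual SD was 1.5. The targeting parameter k sets how strongly alerts concentrate on low users: mean alert contacts are 2·exp(k·U − k²/2), where U is the latent tendency, so the average stays at 2. Models were least squares with country indicators standing in for the random effect. The true effect of implementing telemonitoring is 0.30 throughout.

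Telemonitoring coefficient with all contacts in the model:

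| Targeting k | Case A | Case B | Case C |
|---|---|---|---|
| 0 (none) | 0.095 | 0.005 | 0.195 |
| 0.5 | 0.271 | 0.167 | 0.389 |
| 1.0 | 0.337 | 0.242 | 0.438 |
| 2.0 | 0.143 | 0.029 | 0.252 |

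The first line agrees with the algebra. In the other lines low use drives contacts, so the contact coefficient is itself biased downwards. In case C with k = 1.0 it is −0.069 against a true 0.05. That pushes the telemonitoring coefficient up, in three of the twelve cells to above 0.30.

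Leaving contacts out gave 0.287 to 0.307 over all twelve settings. Adjusting only for scheduled contacts gave 0.288 to 0.308. Scheduled contacts were generated independently of telemonitoring here, so the simulation does not show that the schedule may be ignored. The Introduction describes near-universal telemonitoring in France and names France among countries with several regulated visits a year, so planned visits are a plausible confounder.

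**The case against.** The strongest reply is that the article does not say how frequency is coded or that alert-prompted contacts are counted in it. Mask changes are a separate item in Table 1, so not every provider action need be an interaction. The Introduction speaks of regulated home visits; if frequency means that planned schedule, it is not a consequence of telemonitoring and the problem disappears. Coding, and whether components enter jointly or in steps, could be settled in the analysis plan, which is not shown. This stands as a condition on the point. It does not remove it: Table 1 describes a count of contacts by channel over follow-up, excludes none by origin, and Table 2 lists the components together.

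It is also fair that splitting a bundle into what each component adds given the others is a legitimate analysis. Prompted contacts are still credited, under frequency. The claim about the most effective components is one Discussion sentence, with no ranking procedure behind it. This argues for keeping the four-component model under an accurate label, not for reading its telemonitoring coefficient as the effect of implementation.

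A reader might infer that telemonitoring will always be underestimated, or that a known share of its effect is lost. The documents support neither. The 33% to 100% omitted in the algebra depends on assumed effects and on contacts unrelated to prior use. Alerts plausibly respond to poor use, and then the error can go either way. Nor should the point be carried over in full to the third row, which seeks associations and promises no total effect, or at all to the first row.

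**Conclusion.** The point holds conditionally and for the second row of Table 2. If frequency is the realised contact count and includes alert-prompted contacts, which Table 1 suggests but does not state, the telemonitoring coefficient is an effect at a given number of contacts. It cannot support a statement about what implementing telemonitoring achieves. With contacts unrelated to prior use, it omits the benefit that contacts deliver. With alerts aimed at low users, neither the direction nor the size of the error is known in advance. The illustration (0.005 to 0.438 against a true 0.30 h/day) shows that the discrepancy can be material under the assumed values; it is not an estimate for this study. The issue concerns a secondary objective but bears directly on a conclusion that the study intends payers to use.

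**What to change.** For the second row of Table 2:

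- State how frequency of interactions is coded: planned schedule or realised count.
- Estimate the telemonitoring effect in a model that leaves out realised interactions and adjusts for the selected confounders, country and the visit schedule fixed in advance by regulation or contract. Adjustment for the schedule should not be optional.
- Base any statement on how effective telemonitoring is on that model.
- Keep the four-component model, label its telemonitoring coefficient as the effect at a given number of contacts, and report both.
- Report alert-prompted contacts separately only if the ERP records the origin of a contact; the article describes only channel.

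The cost is one extra model per outcome and a few lines in the analysis plan. Omitting realised interactions needs no new data; the planned schedule would have to be coded from the applicable regulations or contracts. The new estimate will include the contacts that telemonitoring generates, which is intended, and may retain some confounding by planned contact intensity where the schedule is coded coarsely.

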**Sociodemographic and OSA^a^-related clinical characteristics**			
	Demographics (age and sex) BMI	At the start of PAP^b^ therapy	ALH^c^ ERP^d^
	Occupational status and highest education level Sleep characteristics: bed sharing, sleep duration, and sleep medication Smoking status and alcohol consumption BMI	At the time of ePRO^e^ completion	ePRO tool
	Comorbidities: diabetes, stroke, myocardial infarction, coronary stenting or heart surgery, heart failure, cardiac arrhythmia, hypertension, GORD^f^, COPD^g^, asthma, chronic rhinitis, cancer, anxiety or depression, and insomnia	Before starting PAP therapy	ePRO tool
	Apnea-hypopnea index at the time of diagnosis	Before starting PAP therapy	ALH ERP and ePRO tool

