#### Confounding Factors

Potential confounding factors were identified a priori based on a literature review and clinician expertise, and include age, sex, BMI, sleep duration, symptoms before starting PAP therapy, occupational status, highest education level, bed partner, comorbidities, smoking status, alcohol consumption, apnea-hypopnea index at the time of diagnosis, and prescriber specialty. Factors consistently described as being associated with PAP therapy adherence or persistence will be automatically included in statistical models comparing the effect of service on adherence or persistence. Other potential confounding factors will be selected based on their association with adherence or persistence in a univariate analysis. Full details of the confounding variables considered and the supporting sources are provided in Multimedia Appendix 2. Quantitative bias analysis will be performed to evaluate the impact of unmeasured confounders using a metric named the e-value [34]. The e-value can be defined as the strength of association that an unmeasured confounding factor would need to have in order to explain away the observed association.

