### Limitations

Selection bias cannot be entirely ruled out because participants were required to have a valid email address or smartphone number to be eligible for the study. This may lead to underrepresentation of certain subgroups of PAP users, such as older adults. Patients who answer the questionnaire might also differ from those who do not answer it. In addition, this study will only include individuals who use PAP supplied by a home support provider affiliated with ALH and it is possible that the level or content of additional services may differ slightly from other home support providers in the same country. To assess the potential impact of such biases, we will compare the characteristics of our study population with published data on OSA, focusing on age, sex, and disease severity.

Data from the ePRO tool may be subject to recall bias and inaccuracy because participants will complete the web-based questionnaire at variable periods of time since the start of PAP therapy (up to 5 years later for those who started PAP in 2019) and medical data will directly be provided by the patient. Confounding bias other than the key confounding factors considered is another limitation, particularly with respect to medical follow-up (data that will not be collected in this study).

Finally, the period over which this study was conducted included times before and during the COVID-19 pandemic (including lockdowns), and the worldwide recall of a PAP device made by Philips Respironics [36]. Sensitivity analyses will be performed to determine whether these factors had any influence on the overall study findings.

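### Several candidate confounders, notably sleep duration and bed sharing, are timed in Table 1 only at questionnaire completion, after PAP use, and the article does not say which value the service-effect models use

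*Protocol article*

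**What the plan says.** **Candidate confounders.** The Confounding Factors section says the factors "include age, sex, BMI, sleep duration, symptoms before starting PAP therapy, occupational status, highest education level, bed partner, comorbidities, smoking status, alcohol consumption", together with apnea-hypopnea index at diagnosis and prescriber specialty.

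**Entry rules.** There are two. The first is "Factors consistently described as being associated with PAP therapy adherence or persistence will be automatically included in statistical models". For the rest, "Other potential confounding factors will be selected based on their association with adherence or persistence in a univariate analysis". Neither rule asks when the value was measured. The section refers to Multimedia Appendix 2 for details of the individual factors; that appendix is not shown.

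**Timing in Table 1.** One row holds "Occupational status and highest education level" followed by "Sleep characteristics: bed sharing, sleep duration, and sleep medication Smoking status and alcohol consumption BMI", all timed at questionnaire completion. Other rows are timed differently:
- age, sex and a first BMI at the start of PAP, from the provider's ERP system;
- comorbidities and apnea-hypopnea index before PAP;
- symptoms both before and after PAP start.

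**Timing in the text.** Outcome Measures says the questionnaire assesses the patient "at 2 time points: the time of ePRO completion and the beginning of PAP therapy". It then lists, among other items, relationship status, employment, smoking, alcohol and sleep duration.

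**Acknowledged limits.** Limitations concedes that "participants will complete the web-based questionnaire at variable periods of time since the start of PAP therapy", up to 5 years, and names recall bias. It does not discuss using values measured after PAP start as adjustment variables. Sensitivity Analyses covers only the COVID-19 lockdowns and the device recall.

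**The concern.** The article states that it wants the net effect of provider services on adherence and persistence. Adjustment serves that aim when a covariate reflects the patient's state before the service and the PAP use it is meant to influence. A value taken months or years later may itself have been altered by that use. Current sleep duration is the clearest case, since treated patients may sleep longer or differently. Bed sharing may also change once treatment works or fails. Conditioning on such a variable can remove part of the service effect and can open non-causal paths.

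The second entry rule adds to the problem. A variable that PAP use has changed is associated with PAP use for that reason alone, so it is more likely to pass a univariate screen on the outcome. A sample near 100,000 does not reduce this bias; it only makes the biased estimate more precise.

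**Working it through.** The plan gives no figure of its own on this point. The check has three parts.

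**1. Time order.** Inputs: PAP starts run from 1 January 2019 to 31 December 2023 (Process for Selecting Patients). Enrolment began in France in October 2024 (Results). I take 1 October 2024 as the earliest possible questionnaire.
- Last eligible start: 31 December 2023 to 1 October 2024 = 275 days; 275 / 30.44 = 9.0 months.
- First eligible start: 1 January 2019 to 1 October 2024 = 2,100 days; 2,100 / 365.25 = 5.75 years. The article says up to 5 years for 2019 starters, which is about right.

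Adherence is assessed at 1, 4, 6 and 12 months and then annually (Table 1). Every questionnaire therefore follows the 1-, 4- and 6-month outcomes. It also follows the 12-month outcome for anyone who started at least 12 months before completing it.

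**2. The sections side by side.**

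| Candidate confounder | Time point in Table 1 | Covered by the two-time-point text in Outcome Measures? |
|---|---|---|
| Sleep duration | completion only | named |
| Bed partner / bed sharing | completion only | relationship status named, bed sharing not |
| Occupational status | completion only | employment named |
| Smoking, alcohol | completion only | named |
| BMI | start (ERP) and completion (questionnaire) | named |
| Comorbidities | before PAP | named |
| Symptoms before PAP | before and after | named |

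Table 1 separates baseline from current values elsewhere, so its timing for the first four rows looks deliberate. The text points the other way. Its list also contains items that make sense only at completion, such as satisfaction with the provider and current health status, so it does not show that each item has a start-of-PAP version.

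**3. What could follow if completion-time values are used.** All inputs here are assumed; none comes from the documents.

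*(a) Feedback only, no baseline confounding.* Let reported sleep be S = aY + e, with Y the hours of PAP use (SD 2.3 h) and e of SD 1.2 h. The service coefficient adjusted for S is β(1 − ρ²), with ρ² = a²·2.3² / (a²·2.3² + 1.2²).
- a = 0.1: 0.0529 / 1.4929 = 3.5% shrinkage
- a = 0.2: 0.2116 / 1.6516 = 12.8%
- a = 0.3: 0.4761 / 1.9161 = 24.8%
- a = 0.4: 0.8464 / 2.2864 = 37.0%

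*(b) Feedback plus real baseline confounding.* Simulation with n = 1,000,000: baseline covariate C standard normal; service = 1 if N(0,1) + 0.3C > 0; Y = 5 + 0.30·service + 0.4C + noise (SD 2); later value = 0.7C + g(Y − 5) + noise (SD 0.7). The true effect is 0.30 h/day. Unadjusted, the estimate is 0.49 (error +0.19). Adjusted for the baseline value, it is 0.30.

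| g (rise in the later value per h/day of use) | Adjusted for later value only | Error | Adjusted for both values |
|---|---|---|---|
| 0 | 0.40 | +0.10 | 0.30 |
| 0.05 | 0.32 | +0.02 | 0.30 |
| 0.1 | 0.25 | −0.05 | 0.28 |
| 0.2 | 0.11 | −0.19 | 0.23 |
| 0.3 | 0.01 | −0.29 | 0.17 |

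The baseline value is the right one to use, and adding the later value to it only does harm once there is feedback. Where no baseline value exists, the later value is better than nothing when feedback is weak (g up to 0.1), about equal at 0.2, and worse at 0.3.

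**The case against.** The strongest case on the other side has four parts.

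*Entry is conditional.* The factors are called potential confounders, and the appendix with their details is not shown. A reader might infer that the model does adjust for all of them; the article does not say so. This stands.

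*Start-of-PAP values may exist.* Outcome Measures says the questionnaire looks back to the beginning of therapy, and the questionnaire itself is not shown. A reader might infer from Table 1 that only current values are available; that is not established either. This also stands, but it leaves two statements in the article that do not agree, and nothing saying which value is modelled. The point is therefore more than a detail left to the analysis plan.

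*The variables are unlike.* Feedback from PAP use is plausible for sleep duration and bed sharing, and weaker for occupation, smoking and alcohol. The documents show time order, not causation. This stands and narrows the point. Education sits in the same row but is largely fixed in adults.

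*Removing the variables can do harm.* A reader might conclude that every completion-time variable, and recalled symptoms too, should leave the main model. Part (b) of the check shows that omission can bias more than inclusion. Demoting symptoms because they are recalled would also be inconsistent with keeping comorbidities, which come from the same retrospective questionnaire. Limitations already admits the recall problem. This stands and shapes the fix.

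**Conclusion.** The point holds in a conditional form. Table 1 and Outcome Measures disagree on whether start-of-PAP values exist for these candidate confounders, and the article does not say which value enters the service-effect models. If completion-time values are used, they are measured at least 9 months after PAP start and after the early outcomes. The models may then adjust for variables partly changed by PAP use, chiefly sleep duration and bed sharing, and the univariate screen favours exactly such variables.

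No size or direction can be set from the documents. The 4% to 37% shrinkage in part (a) should not be read as an estimate: it rests on assumed inputs and on no baseline confounding. With such confounding, the error in part (b) ran from +0.10 to −0.29 h/day around a true 0.30, again on assumed inputs. A claim that the model does adjust for consequences of the outcome would go further than the text allows.

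**What to change.** 1. Reconcile Table 1 with Outcome Measures: for each candidate confounder, state whether a start-of-PAP value, a completion value or both are collected.
2. Specify that the main models use the start-of-PAP value wherever the ERP system or the questionnaire provides it. For BMI, that is the ERP value at start, not current BMI.
3. Where sleep duration or bed sharing exists only at completion, do not let it enter the main model through univariate selection.
4. As a sensitivity analysis, report the service effect with and without all completion-only covariates, and repeat it in 2023 starters, whose lag is shortest (at 1 October 2024, from 275 days to 365 + 274 = 639 days, or 9 months to 1.75 years).
5. Keep pre-PAP symptoms and comorbidities in the main set, with the recall limitation already stated.

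The cost is some plan wording and a little more analysis. Where no start-of-PAP value exists, leaving a variable out may allow residual confounding; the gap between the paired models would show how much depends on it.
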